Interscalene brachial plexus block (ISB) is currently the first-line opioid-sparing analgesic regimen for shoulder surgery, as it significantly reduces postoperative pain scores, improves patient satisfaction, and shortens hospital stay (17). Nevertheless, ISB has a critical and potentially life-threatening limitation: it is associated with a more than 90% incidence of ipsilateral hemidiaphragmatic paresis (HDP). [18–20]HDP leads to a 27% reduction in forced vital capacity (FVC) and forced expiratory volume in 1 s (FEV1), which is intolerable for patients with preexisting pulmonary dysfunction, who may develop life-threatening hypoxemia and respiratory distress after HDP occurs (18, 19). Paradoxically, these high-risk patients are also not candidates for general anesthesia alone, as anesthetics, analgesics, and muscle relaxants can further impair their respiratory function and worsen clinical outcomes (20, 21).

To reduce the risk of HDP, various modified nerve block techniques have been explored, including low-volume ISB, costoclavicular block, combined axillary and suprascapular nerve block and anterior shoulder capsule block. However, even low-dose ISB still has an HDP incidence of over 20%, and costoclavicular block, initially reported to have zero HDP risk, has been verified to have an HDP rate ranging from 7.5 to 50% in subsequent studies including our team’s previous work (22–24). Other aforementioned modified techniques remain clinically controversial, with multiple studies reporting insufficient pain control for arthroscopic shoulder surgery and high rates of rescue analgesia (25, 26). Recently, Zhang et al. reported that subparaneural injection of 5 mL ropivacaine at the bifurcation of the brachial plexus upper trunk achieved non-inferior analgesia compared with ISB, while reducing the HDP incidence to 16.7% (27). While this finding is promising, the 16.7% HDP risk is still unacceptable for patients with severe pulmonary impairment, as even minimal risk of HDP can lead to catastrophic clinical outcomes, following the “all-or-none” principle of HDP prevention (21). The minimal effective volume of local anesthetic for this technique, which could eliminate HDP risk while maintaining satisfactory analgesia, remains undefined.

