#### General anesthesia recovery

At the completion of the surgical procedure, the inhaled sevoflurane is discontinued immediately, and the fresh gas flow is increased to 6 L/min to accelerate the washout of the anesthetic agent from the patient’s body. Mechanical ventilation is maintained with settings consistent with those described in the general anesthesia induction section, without modifications, until spontaneous breathing is fully restored.

Extubation of the LMA is performed only when all the following extubation criteria are met: the patient regains full consciousness and can follow verbal commands; spontaneous breathing is stable, with a tidal volume ≥ 6 mL/kg predicted body weight and respiratory rate of 10–20 breaths per minute; EtCO₂ is maintained between 35 and 45 mmHg; the gag and cough reflexes are fully recovered; heart rate and mean arterial pressure remain within 20% of the preoperative baseline; and SpO₂ ≥ 95% is maintained on room air. After LMA removal, the patient is given supplemental oxygen via a face mask at 4 L/min, and transferred to the PACU accompanied by the attending anesthesiologist responsible for anesthesia management.

Upon arrival in the PACU, standard continuous monitoring is initiated immediately, including three-lead ECG, NIBP measured at 5-min intervals, continuous SpO₂, and respiratory rate monitoring. The patient’s level of consciousness, respiratory status, surgical site condition, and adverse events are assessed and documented every 15 min by PACU nursing staff who remain fully blinded to the subject’s group allocation throughout the recovery period.

Pain assessment is performed immediately after the patient regains full consciousness and can accurately report discomfort. Pain intensity is scored based on the patient’s self-reported arm or shoulder discomfort using the 11-point Numerical Rating Scale (NRS), where 0 represents no pain and 10 indicates the greatest anguish imaginable. All recorded NRS scores are the pre-rescue analgesia values. If the patient’s NRS score is greater than 3, an intravenous bolus of 5 μg sufentanil is administered, and this administration is repeated as required to achieve adequate pain control. The exact time, dose, and number of fentanyl boluses administered in the PACU are fully documented in the electronic anesthesia record system.

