### Data collection

All study data are collected at pre-specified time points in accordance with the study protocol, with the specific collection content as follows:

*Screening and baseline data*: Subject demographic information (age, gender, height, weight, BMI), ASA physical status classification, preoperative comorbidities (hypertension, diabetes, cardiovascular disease, chronic pulmonary disease, etc.), past medical history (ipsilateral shoulder or cervical surgery history, chronic pain history, allergy history), preoperative vital signs (heart rate, blood pressure, SpO₂), preoperative laboratory test results (hemoglobin, platelet count, coagulation function, liver and kidney function), and preoperative pulmonary function and diaphragmatic excursion baseline measurements (FEV1, FVC, FEV1/FVC ratio, ipsilateral diaphragmatic excursion value).*Intraoperative data*: general anesthesia related data (induction and maintenance drug dosage, anesthesia duration, surgery duration, laryngeal mask airway extubation time, emergence time), intraoperative hemodynamic parameters, total dosage of intraoperative analgesic and vasoactive drugs, intraoperative fluid balance (infusion volume, blood loss, urine output), and any protocol deviations or adverse events during the operation.*Post-anesthesia care unit (PACU) data*: Pre-rescue analgesia NRS pain score assessed immediately after the patient regains full consciousness from general anesthesia (before rescue analgesia in PACU), postoperative diaphragmatic excursion and pulmonary function measurements, PACU stay duration, rescue analgesia administration details, emergence and recovery related indicators, and any adverse events during the PACU stay.*Safety and compliance data*: Detailed records of all perioperative adverse events and serious adverse events, including onset time, severity, causal relationship with the study intervention, treatment measures, and final outcome; detailed records of subject withdrawal, loss to follow-up, and protocol deviations, including specific reasons and corresponding handling measures.

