#### Secondary outcomes

1 Diaphragmatic function parameters

Absolute value of ipsilateral diaphragmatic excursion before discharge from the PACUAbsolute and percentage changes in ipsilateral diaphragmatic excursion from preoperative baseline to PACU discharge

2 Pulmonary function parameters

Absolute values of forced expiratory volume in 1 s (FEV1) and forced vital capacity (FVC) before discharge from the PACUAbsolute and percentage changes in FEV1 and FVC from preoperative baseline to PACU discharge

3 Upper extremity sensorimotor block characteristics

Sensory block scores of the radial, median, ulnar, musculocutaneous and axillary nerves before discharge from the PACU (0 = no block; 1 = analgesia, intact touch sensation but absent cold sensation; 2 = anesthesia, absent touch sensation)Motor block scores of the radial, median, ulnar, musculocutaneous and axillary nerves before discharge from the PACU (0 = normal movement; 1 = partial paralysis; 2 = complete paralysis)

4 Perioperative analgesic drug consumption

Total intraoperative sufentanil dosageTotal sufentanil dosage administered for rescue analgesia in the PACU

5 Recovery-related indicators

Total time interval from completion of nerve block to PACU dischargeSurgical durationPACU stay durationPostoperative hospital length of stay

6 Safety indicators

Incidence of all perioperative adverse events, including nausea, vomiting, pruritus, hypotension, bradycardia, local anesthetic toxicity, nerve injury, Horner syndrome, hoarseness and dyspneaIncidence of serious adverse events related to the study intervention, including severe respiratory distress, anaphylactic reaction and permanent neurological deficitIncidence of protocol deviations and subject withdrawal/loss to follow-up, with detailed documentation of specific reasons

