##### Analysis of secondary outcomes

*Continuous variables*: Normally distributed data (e.g., diaphragmatic excursion, FEV1, FVC, emergence time, PACU stay duration) will be presented as mean ± standard deviation (SD), and between-group differences will be analyzed using the two-sample t-test. Non-normally distributed data (e.g., analgesic drug consumption, postoperative hospital length of stay) will be presented as median (interquartile range, IQR), and between-group differences will be analyzed using the Mann–Whitney U test.*Categorical variables*: Data will be presented as counts (percentages). Between-group comparisons will be performed using the chi-square (χ^2^) test for large sample sizes or Fisher’s exact test for cell counts < 5.*Ordinal variables* (e.g., sensory and motor block scores): Between-group differences will be analyzed using the Mann–Whitney U test.

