##### Multiplicity adjustment

No multiplicity adjustment will be performed for the two co-primary endpoints, as they address distinct and independent research questions (analgesic efficacy vs. diaphragmatic safety), and both must be statistically significant to declare the overall success of the trial.All secondary outcomes are exploratory in nature and will not undergo multiplicity adjustment. Results will be presented with point estimates and 95% CIs, and *p* values will be interpreted descriptively rather than as definitive hypothesis tests.

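### PACU rescue is summarised as a median dose that will probably read 0 (0–0) in both arms, so the proportion of patients needing rescue is never estimated

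*Protocol article*

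**What the plan says.** Item 4 of Secondary outcomes names the total "sufentanil dosage administered for rescue analgesia in the PACU". Neither the secondary outcomes nor the sensitivity analyses include the proportion of patients rescued, or the proportion with NRS above 3.

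Analysis of secondary outcomes gives analgesic consumption as an example of non-normal data: "Non-normally distributed data (e.g., analgesic drug consumption, postoperative hospital length of stay) will be presented as median (interquartile range, IQR"). The same sentence sets the Mann–Whitney U test for the comparison between arms. Multiplicity adjustment adds, for all secondary outcomes: "Results will be presented with point estimates and 95% CIs", with p values read descriptively.

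General anesthesia recovery sets the trigger: if the "NRS score is greater than 3, an intravenous bolus of 5 μg sufentanil is administered", repeated as needed. It also states: "All recorded NRS scores are the pre-rescue analgesia values". Data collection includes "rescue analgesia administration details" among the PACU data.

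The primary analgesic analysis compares mean pre-rescue NRS by an equal-variance t-test against a 1-point margin.

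**The concern.** Rescue dose after an effective block is a variable with many zeros. What a reader most wants from it is how many patients needed rescue in each arm. A median with quartiles cannot show this until about a quarter of an arm has been rescued.

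The Introduction discounts rival techniques for "insufficient pain control for arthroscopic shoulder surgery and high rates of rescue analgesia", but the plan does not estimate that rate for its own two arms. If the smaller volume sometimes fails in individual patients, the excess would appear as a few extra rescued patients. The published table could then show identical rescue summaries beside a non-inferior mean NRS, with no estimate of the excess.

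**Working it through.** **The plan's own figure.** Inputs from the NRS sample size section: SD 1.6, margin 1, one-sided alpha 0.025, power 0.80.

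n = 2 × (1.96 + 0.84)² × 1.6² / 1² = 40.14, stated as 40 per arm. With 20% dropout, 40 / 0.8 = 50 per arm. The figure reproduces.

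**When the summary stops reading 0 (0–0).** The upper quartile is above zero only once enough patients have a non-zero dose. Across common quantile definitions this takes 12–13 rescued of 50 (24–26%), or 10–11 of 40 (25–27.5%). The median stays 0 until about half are rescued.

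**What the promised estimate would show.** Take 5/50 rescued against 0/50. Both arms read 0 (0–0), and the difference in medians is 0. A shift estimate based on pairwise differences is also 0, because 0.90 × 1.00 = 90% of the pairs are tied at zero.

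As a proportion, the same data read 10% against 0%. The Wilson limits are 4.35–21.36% and 0–7.13%, so the Newcombe 95% CI for the difference is:
- lower: 0.10 − √[(0.10 − 0.0435)² + 0.0713²] = 0.009
- upper: 0.10 + (0.2136 − 0.10) = 0.214

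That is a difference of 10 points, CI about 1 to 21.

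**What the Mann–Whitney test sees.** With one 5 μg bolus per rescued patient, the tie-corrected statistic (no continuity correction) reduces to z² = (N − 1)(ad − bc)² / (product of the four margins). For 4 against 0 of 50: 99 × (4 × 50)² / (50 × 50 × 4 × 96) = 4.125, so z = 2.03 and p = 0.042. Likewise 7 vs 1 gives p = 0.028 and 8 vs 2 gives p = 0.047. Simulated power is about 74% at true rates of 10% vs 0% and 95% at 15% vs 0%. It is only about 15% at 10% vs 5% and 39% at 15% vs 5%.

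**What the primary endpoint sees.** At SD 1.6 and 50 per arm, non-inferiority needs an observed mean difference below 1 − 1.984 × 1.6 × √(2/50) = 0.365.

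Simulation, 50 per arm. The score distributions are assumptions, since the protocol gives none: working blocks score 0/1/2/3 with probabilities 0.35/0.30/0.20/0.15, failed blocks score 4–8 uniformly, and the dose is 5 or 10 μg if the score exceeds 3. The last column is the share of trials in which non-inferiority passes, both arms read 0 (0–0) and Mann–Whitney p ≥ 0.05.

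| True failure rate, 2 mL vs 5 mL | Non-inferiority passes | All three together |
|---|---|---|
| 10% vs 0% | 42% | 21% |
| 12% vs 2% | 36% | 29% |
| 10% vs 5% | – | 59% |
| 15% vs 0% | 9–16%* | 3% |
| 20% vs 0% | about 4% | under 1% |

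*Range over the score distributions tried.

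At 10% vs 0% and 12% vs 2%, both arms read 0 (0–0) in every trial that passed. With 40 evaluable per arm, the last column becomes 28%, 28% and 52% for the first three rows. A second set of score distributions (working blocks 0–3 with mean 0.6 or 1.5, failures 5–8) gives joint figures at 50 per arm of 67–69% at 5% vs 0%, 21–22% at 10% vs 0%, 50–55% at 10% vs 5%, 20–25% at 15% vs 5% and 4% at 15% vs 0%.

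**Is rescue likely to be below a quarter?** This depends on the mean NRS. Taking scores as normal with SD 1.6 and cutting at 3.5, the rescue rate is 1 − Φ((3.5 − mean)/1.6): about 3% at a mean of 0.5, 11% at 1.5, 17% at 2, 27% at 2.5 and 38% at 3.

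**The case against.** The strongest reply is that the plan already looks at rescue and block failure in several ways.

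- The sentence that sets the median (IQR) also sets a Mann–Whitney test. With few dose levels, that test is close to a comparison of rescued with not rescued. This stands: it would be wrong to say that rescue is analysed only as a median. However, the protocol reads secondary p values descriptively, and a small p beside two identical 0 (0–0) entries does not tell the reader how large the excess is.
- The primary NRS is taken before rescue, so each failed block enters the mean at its full score. This also stands. A reader might infer that outright failures stay hidden at any rate below a quarter, for example at one patient in five. The table does not support that: at 20% vs 0% non-inferiority passes in about 4% of trials, and all three conditions coincide in under 1%.
- A reader might also infer that passing at 10% vs 0% is a false claim of non-inferiority. It is not. The working-block mean is 1.15 and the failed-block mean is 6, so the true mean difference is 0.10 × 4.85 = 0.485, inside the 1-point margin. The verdict is right for the endpoint chosen; it just does not describe the tail.
- Sensory and motor block scores and intraoperative sufentanil are also compared, and would give some signal of failed blocks. They do not say how many patients needed rescue.
- An unseen analysis plan may add a rescue count. That is possible, but the protocol is not silent here: it fixes the outcome, the summary and the test. That the smaller volume fails in a few patients rather than by a uniform shift is plausible but not stated in the protocol.

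**Conclusion.** The point holds as a weakness in the chosen summary, not as an error in the primary analysis. As stated, the rescue outcome will read 0 (0–0) in any arm with fewer than about 24–26% rescued, the accompanying difference will be 0, and the rescue rate goes unestimated.

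The range exposed is a modest excess of about 5–10 percentage points in the 2 mL arm. There, a passing mean NRS, identical rescue summaries and a non-significant rank test coincide in roughly 20–70% of simulated trials, depending on the rates in the two arms. Larger excesses are mostly caught by the primary endpoint or the rank test.

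These sizes rest on assumed score distributions and on a mean NRS of about 2 or lower. At a mean of 2.5 or more, rescue would pass a quarter and the upper quartile would start to show it.

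**What to change.** Keep total PACU sufentanil dose with its Mann–Whitney test. Beside it, add the number and percentage in each arm with any PACU rescue sufentanil (under the stated trigger, in effect pre-rescue NRS above 3), with the risk difference and a score or exact 95% CI. Report this next to the non-inferiority result. The gain is an interpretable estimate rather than another test.

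Also give the arm mean dose, which does not collapse to zero. Dose among those rescued may be shown for description only: it conditions on an event after randomisation, so the arms are no longer a randomised comparison.

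The cost is a few lines of wording. The pre-rescue score and rescue details are already recorded, and sample size, alpha and the rescue rule do not change.

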##### Multiplicity adjustment

No multiplicity adjustment will be performed for the two co-primary endpoints, as they address distinct and independent research questions (analgesic efficacy vs. diaphragmatic safety), and both must be statistically significant to declare the overall success of the trial.All secondary outcomes are exploratory in nature and will not undergo multiplicity adjustment. Results will be presented with point estimates and 95% CIs, and *p* values will be interpreted descriptively rather than as definitive hypothesis tests.

##### Sensitivity analyses

To verify the robustness of the primary findings, the following sensitivity analyses will be performed:

Re-analysis of both co-primary endpoints using the PP populationRe-analysis of the non-inferiority endpoint using the non-parametric Mann–Whitney U test to account for potential non-normality of NRS pain scoresRe-analysis of the HDP incidence endpoint using Fisher’s exact testComplete-case analysis of primary outcomes without imputation of missing dataOutlier sensitivity analysis: outliers of the total time interval from nerve block completion to PACU discharge (defined as values outside mean ± 3 standard deviations) will be excluded, and the co-primary endpoints will be re-analyzed to verify the stability of the resultsStratified subgroup analysis: if a significant intergroup difference in the total time interval is detected, subgroup analysis stratified by the median of the time interval will be performed for the co-primary endpoints, to explore the influence of this factor on the study results

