Discharge from the PACU is only permitted when the patient meets all the following criteria: the Aldrete recovery score is ≥ 9 points; core body temperature is maintained at 36.0–37.5 °C; hemodynamic and respiratory status are stable for at least 30 min without supplemental oxygen support; pain is well controlled with a NRS pain score ≤ 3; no severe adverse events such as persistent nausea and vomiting, dyspnea, or neurological abnormalities are observed; the required postoperative pulmonary function and diaphragmatic excursion assessments have been fully completed; and the PCA pump has been correctly initiated. All recovery-related data, including emergence time, LMA extubation time, PACU stay duration, vital signs during recovery, adverse events, and rescue analgesia administration, are fully documented in the electronic anesthesia record system and study-specific case report form (CRF) in real time.

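### The planned median split of both co-primaries on block-to-PACU-discharge time conditions on a partial consequence of those outcomes and can shrink the NRS difference spuriously; the ±3 SD exclusion on the same interval is only a weak stability check

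*Protocol article*

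**What the plan says.** Two of the listed sensitivity analyses use the time from block completion to PACU discharge, and both re-analyse both co-primary endpoints.

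- **Exclusion.** The plan says "outliers of the total time interval from nerve block completion to PACU discharge (defined as values outside mean ± 3 standard deviations) will be excluded". Its stated aim is to check that the results are stable.
- **Median split.** The plan says "subgroup analysis stratified by the median of the time interval will be performed for the co-primary endpoints", conditional on the clause "if a significant intergroup difference in the total time interval is detected". Its stated aim is to explore the influence of time.

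Both stand under a general sentence about verifying the robustness of the primary findings. Secondary outcomes lists the same interval among the recovery indicators.

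General anesthesia recovery sets out what ends the interval. An NRS above 3 leads to sufentanil, repeated as needed. Discharge then requires, among other things, that "pain is well controlled with a NRS pain score ≤ 3", that "hemodynamic and respiratory status are stable for at least 30 min without supplemental oxygen support" and that "no severe adverse events such as persistent nausea and vomiting, dyspnea, or neurological abnormalities are observed". It also requires an Aldrete score of at least 9, normal temperature, completed lung and diaphragm tests, and a started PCA pump.

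**The concern.** A sensitivity analysis should ask the primary question again under a different assumption. A split on a variable that follows the outcome asks a different question. A patient who wakes with a high NRS needs rescue and cannot leave until the score is 3 or less, so that patient tends to fall in the long-time half. The short-time half is then enriched for patients with low scores in both arms, and the arms look more alike than they are. In a non-inferiority comparison that error favours the new regimen. The randomised comparison is also lost, because membership of a half depends partly on the result.

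Nor can discharge time explain an NRS that was already recorded before discharge. If the arms do differ on the interval, pain or breathing may be the reason, and the split cannot separate that from an effect of time since the block.

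**Working it through.** **Order of events (Primary outcomes; General anesthesia recovery; Postoperative pulmonary function test and diaphragmatic excursion measurement).** Block, surgery, NRS on regaining consciousness and before rescue, rescue if NRS is above 3, diaphragm scan before discharge, discharge. The interval closes after both co-primary measurements.

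**Inputs from the protocol.** 50 per arm, NRS SD 1.6, margin 1, one-sided α 0.025, HDP 16.67% against about 0. The plan's sample size formula gives 2 × (1.96 + 0.84)² × 1.6² / 1² = 2 × 7.84 × 2.56 = 40.14, stated as 40, and 40 / (1 − 0.20) = 50. This point disputes neither figure.

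**Assumed inputs (not in the protocol).** True NRS difference at the margin, about 1.0, so every declaration of non-inferiority is false; 5 mL mean 3. Interval = other time + b × max(NRS − 3, 0), with b = 10, 20 or 30 min and SD of other time 25 or 60 min.

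**Precision.** The CI half-width is t × 1.6 × √(1/n₁ + 1/n₂). For 50 and 50 it is 1.984 × 1.6 × 0.2 = 0.64. For 25 and 25 it is 2.011 × 1.6 × 0.283 = 0.91.

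**Median split, short-time half, by simulation.**

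| b (min per point) | NRS difference, SD 25 | NRS difference, SD 60 | False non-inferiority, SD 25 |
|---|---|---|---|
| 10 | 0.73 | 0.90 | 9.4% |
| 20 | 0.58 | 0.78 | 21.2% |
| 30 | 0.49 | 0.69 | 32.6% |

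With b = 0 the short half gives 0.99, so the shrinkage comes from the dependence of time on pain. Over both SDs, false non-inferiority in the short half is about 4 to 33%; in the full set it is 2.6 to 3.4%. In a separate run with SD 25, the long half gave 1.08, 0.96 and 0.82 for b = 10, 20 and 30, so the long half does not reliably offset the short one.

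**HDP and other time distributions.** A second set of runs added a delay for HDP of 15 to 60 min and for rescue of 10 to 20 min, with 5 to 15 min per NRS point, SD 20 or 40 min, and normal or right-skewed other time. The true HDP risk difference of 0.167 became 0.00 to 0.13 in the short half and 0.21 to 0.36 in the long half. The short-half NRS difference was 0.86 down to 0.44, with false non-inferiority of 4.4 to 45%.

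**Significance trigger.** Short-half false non-inferiority with SD 25 was 8.4%, 18.8% and 31.1% in trials that met the trigger, against 9.4%, 21.2% and 32.6% in all trials.

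**±3 SD exclusion.** It removed 0.2 to 1.8 patients on average. False non-inferiority was 2.5 to 3.6% across the two sets of runs, against 2.6 to 3.4% without exclusion. In the second set the conclusion changed in at most 0.7% of trials. A single data set can still move:

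- Removing two patients with NRS 8 from a 50-patient arm with mean 3 lowers that mean by 2 × (8 − 3) / 48 = 0.21, against a half-width of 0.64.
- With HDP in 8/50 (5 mL) and 3/50 (2 mL), the lower limit is 0.100 − 1.96 × √(0.16 × 0.84/50 + 0.06 × 0.94/50) = −0.021. Removing one long-stay HDP case from the 2 mL arm gives 8/50 and 2/49, with lower limit +0.003.

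**The case against.** The strongest reply is that nothing decisive hangs on these analyses. Success rests on the ITT analyses, which do not condition on the interval. The split is conditional, is described as exploratory and carries no decision rule. A split also reports both halves, and in trials that met the trigger both halves showed non-inferiority in at most 0.9%. A false primary result, a met trigger and an agreeing short half occurred together in at most 0.15%. This stands, and it limits the severity.

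The delays are assumed, and the interval contains induction, the whole operation, emergence and several discharge steps unrelated to pain. That also stands. More unrelated variation weakens the bias, as the SD 60 column shows, but does not remove it. For HDP the distortion needs affected patients to be kept longer, which may be uncommon in a population from which FEV1/FVC below 70% is excluded.

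Three stronger readings are tempting and not supported:

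- **That the ±3 SD exclusion also manufactures non-inferiority.** The runs show no material inflation.
- **That the significance trigger makes the bias worse.** The short-half error was no higher in triggered trials. The objection to the trigger is one of interpretation: it calls for the split when treatment may itself be acting on the interval.
- **That pain and breathing alone fix the interval.** The discharge list and the surgical time show that they determine it only in part.

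**Conclusion.** The point holds for the median split. The interval is a post-randomisation outcome that closes after both co-primary measurements, and the protocol's own rescue and discharge rules tie its end to pain and breathing. That much follows from the text. The size does not: a short-half NRS difference of about 0.5 to 0.9 where the truth is about 1.0, and false non-inferiority of about 4 to 33% against about 3%, hold only for 10 to 30 min per NRS point above 3 and other-time SD of 25 to 60 min. The HDP distortion is conditional on HDP delaying discharge.

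The ±3 SD exclusion has a different and smaller fault. It drops about 0 to 2 patients, chosen partly by outcome, and almost never alters the conclusion, so an unchanged result is weak evidence of stability.

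A reader might infer that the trial's main conclusion is at risk. It is not, because the primary ITT analyses and the success rule are untouched. The severity is minor, though the change should be made, since a favourable short-time half could be reported as support for robustness that it does not give.

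**What to change.** Delete the significance-triggered median split, and drop the ±3 SD exclusion as a stability check.

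If the influence of time since the block is of interest, which is reasonable because the block may change before assessment, use time from block completion to the NRS assessment for pain and to the diaphragm scan for HDP. Each ends at the measurement it is meant to explain. Enter it as a covariate in a regression on all patients, without cutting the sample.

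Label that regression supportive and exploratory. These times also arise after randomisation: emergence may depend on intraoperative sufentanil and sevoflurane given when the block is inadequate, and rescue may delay the scan. Adjustment could therefore remove part of a treatment effect, and the report should say so.

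The cost is a wording change before database lock, two recorded clock times per patient and that caveat. Ultrasound images are already archived in real time, which should help with the scan time.
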